## Abstract

**Background:**

Specific blends of essential amino acids (EAA) containing a high percentage of branched-chain amino acids preserves mitochondrial metabolism and higher physical resistance in elderly mice, increasing their survival and improving physical performance and cognitive functions in malnourished elderly patients. However, no study has been yet done on patients with anorexia nervosa (AN) who regain weight with specialized intensive treatment. The present study aims to evaluate the efficacy of supplementation with EAA on the change in lean body mass (LBM) and other physical and psychological outcomes in patients with AN who are undergoing specialist treatment for eating disorders.

**Methods:**

This is a 13-week randomized, double-blind, placebo-controlled study. Patients will be randomized to either a mixture of a complex blend of EAA and intermediates of the tricarboxylic acid (TCA) cycle (citrate, malate, succinate) supplementation (or placebo) upon admission at the intensive residential and day-hospital treatment for eating disorders. Ninety-two participants with AN aged 16–50 years will be recruited from a specialized intensive treatment of eating disorders. Double-blind assessment will be conducted at baseline (T0) and the end of the 13 weeks of treatment (T1). The study’s primary aim is to evaluate the efficacy of supplementation with EAA and TCA intermediates on the change in lean body mass (LBM) with weight restoration in patients with AN who are undergoing specialist treatment for eating disorders. The secondary aims of the study are to assess the effect of dietary supplementation on physical fitness, weight restoration, modification of AN and general psychopathology, and psychosocial impairment.

**Discussion:**

The study’s results will inform researchers and clinicians on whether supplementing a mixture of EAA and TCA cycle intermediates will improve the increase of LBM and other important physical and psychological outcomes in patients with AN who regain weight with specialized intensive treatment.

**Trial registration:**

NCT, NCT05290285. Registered on 22 March 2022.

## Introduction

### Background and rationale {6a}

Anorexia nervosa (AN) is a severe eating disorder (ED) characterized by restriction of energy intake relative to requirement, leading to a significantly low weight, overvaluation of shape and weight, and persistent lack of recognition of the seriousness of the current low body weight. It has the highest mortality rate among all psychiatric diseases [1]. Multidisciplinary treatment incorporating medical, psychological, and nutritional interventions is the best practice for these patients [2, 3]. However, the underlying pathophysiology is unclear, and the outcome of recommended treatments is often unsatisfactory [4]. A recent systematic meta-review of meta-analyses and network meta-analyses has confirmed that no medication effectively reduces ED and general psychopathology and improves weight outcome in patients with AN [5]. These data support previous evidence that drugs cannot be recommended to improve body weight or specific psychopathology [4, 6] unless psychiatric comorbidity is present. On the other hand, weight restoration and the recovery of a normal nutritional status are key effective elements in the treatment of AN [7, 8], similarly to muscle and cognitive function improvement [9].

Assessment of nutritional aspects is crucial in the treatment of AN because evidence has shown that even beyond weight restoration, patients continue to show nutritional insufficiencies [10], a more limited spectrum of food preferences [11], and restricted dietary intake [12]. A recent systematic review and assessment of evidence quality on dietetic interventions for adult outpatients with an ED concluded that across the studies examining participants with AN, there was poor quality of evidence for the majority of outcomes measured (i.e., weight, ED behaviors, and psychopathology). They concluded that it is currently problematic for ED clinicians to draw firm conclusions about what should be enclosed in dietetic treatment for outpatients with AN [13].

On the other hand, nutrition is one of the significant determinants of health, particularly in AN. Among the three primary macronutrients, proteins—in particular, their quantity and quality (i.e., their specific amino acid profile)—play a crucial role in regulating metabolic health and longevity. Amino acids (AAs) are essential not only for protein synthesis and influencing nutritional status but also as sources of vital elements (e.g., nucleotides, neurotransmitters) and as signal molecules for the modulation of gene expression and epigenetic mechanisms [14].

Chronic food supplementation with a specific blend of essential amino acids (EAA) containing a high percentage of branched-chain amino acids (leucine, isoleucine, valine) preserves mitochondrial metabolism and greater physical resistance in elderly mice, increasing their survival [15]. Amino acid mixtures can also counteract the functional atrophy of skeletal muscles in elderly and cachectic or sarcopenic individuals [16, 17].

We have recently demonstrated the greater efficacy of new EAA blends enriched with intermediates of the Krebs cycle on energy metabolism [18]. In particular, we found a beneficial effect on physical and cognitive performance in SAMP8 mice supplemented with a specific EAA formula enriched with Krebs cycle intermediates (PD-E07) [19]. This mouse model of functional decline related to the age of skeletal muscle and impaired working memory is widely used to evaluate pharmacological, nutritional, or exercise efficacy. It has been shown that the PD-E07 formula, administered orally with drinking water (1.5 mg/kg) in addition to the regular diet, improves muscular and cognitive performance after 3 months of treatment, promoting mitochondrial rejuvenation in the striated muscles and hippocampus.

More specifically in humans, a recent randomized study was conducted for 2 months, in a double-blind, on 155 malnourished older adults (aged > 80 years), in which a group of patients (*N* = 78) received a dietary supplement with a specific formula of EAA (8 g / day) plus nutritional advice and one group (*N* = 77) received placebo plus nutritional advice. The study found that the EAA supplement increased physical performance and improved cognitive functions in malnourished elderly patients by promoting the bioenergetics of mitochondria in circulating peripheral blood mononuclear cells (PBMCs) [20].

To our knowledge, only one study has been conducted with AA on patients with AN. The study, a double-blind, randomized controlled trial, had a duration of 3 weeks and evaluated the effect of the semi-essential amino acid L-tyrosine (100 mg/kg/day) versus a placebo supplement on cognition and emotional state in 19 female patients with severe and long-lasting AN treated in a hospital setting [21]. Tyrosine shortened reaction time and test duration in memory tasks and improved depressive mood. No side effects have been reported with the use of tyrosine. To date, no studies have evaluated the effect of supplementation with AAs in patients with AN managed with a treatment aimed to address weight restoration and the remission of the eating disorder psychopathology.

We hypothesize that patients with AN receiving the AminoTher-Pro™ product (corresponding to PD-E07; hereafter, AmT-P) compared to those who receive a placebo will achieve the following at the end of the treatment: (i) a higher percentage increase in LBM; (ii) a more significant improvement in physical fitness; (iii) a more significant reduction in ED psychopathology, general psychopathology, and psychosocial injury secondary to the ED; and (iv) a more significant change in the bioenergetic functions in PBMCs, circulating metabolites, and metagenomic profile of the fecal microbiome.

### Objectives {7}

The study aims to compare the efficacy of dietary supplementation with the designer product (AmT-P)—compounded by an original EAA mixture and TCA cycle intermediates with precise stoichiometric ratios—to placebo on LBM modifications obtained with weight restoration in AN patients undergoing a specialist ED treatment.

The secondary aims of the study are to assess the efficacy of the dietary supplement in improving physical fitness, weight regains, modification of ED and general psychopathology, and psychosocial impairment, compared to placebo supplementation.

### Trial design {8}

This study is a randomized, double-blind, placebo-controlled superiority trial. Patients will be randomized to either AmT-P or placebo supplementation upon admission to the treatment. Randomization is carried out at the hospital entry by adopting a stratification for the following parameters: (i) age (16–50); and (ii) body mass index (BMI) (BMI > 14 kg/m^2^). The treatment lasts 13 weeks.

## Methods: participants, interventions, and outcomes

### Study setting {9}

The study will be performed at the Department of Eating and Weight Disorder of the Villa Garda Hospital (Garda, Italy), a community clinic accredited with the Italian National Health System for the inpatient and day-hospital rehabilitation treatment of eating disorders.

### Eligibility criteria {10}

Participants meeting the following criteria will be included in the trial: diagnosis of AN, age between 16 and 50 years, and written informed consent.

Exclusion criteria are as follows: schizophrenia or other psychotic disorders, bulimia nervosa, substance use disorder, medical complications that are potentially capable of hindering the interpretation of the results (e.g., a medical disease that induces weight loss), presence of physical treatments (including drugs) that are potentially able to hinder the interpretation of the results (e.g., chemotherapy for cancer), and pregnancy or intention to become pregnant during treatment.

The study will be performed by medical doctors, psychotherapists, and dietitians.

### Who will take informed consent? {26a}

The physicians of the ED unit will obtain informed consent or assent from potential trial participants or authorized surrogates. Informed consent will be given verbally and in writing, dated and signed by the subject, or in the case of a minor patient, by their parents and/or legal guardians.

### Additional consent provisions for collection and use of participant data and biological specimens {26b}

Not applicable. We have described the terms of collection and use of participant data and biospecimens in the informed consent.

## Interventions

### Explanation for the choice of comparators {6b}

Participants will be randomized to the experimental formula AmT-P or placebo. An inert placebo is the correct comparator as the research serves to establish the safety and the efficacy is unknown. Future trials may include active comparators if collected data suggest clinical benefit. Placebo is an isocaloric product containing maltodextrins rather than AAs [22].

### Intervention description {11a}

The composition of the AmT-P mixture (AminoTher-Pro™, Professional Dietetics S.p.A., Milan, Italy, Italian food supplements register code 95,457) is shown in Table 1. The AmT-P blend will be administered orally at 4.5 g twice daily (two sachets per day).

**Table 1 Tab1:** Composition of the amino acid mixture (PD-E07/AminoThe-Pro^TM^)

	PD-E07/AminoTher-PRO^TM^		
	1 sachet (g)	2 sachets (g)	g/100
l-Leucine	1.2	2.4	23.5
l-Lysine (chlorhydrate)	0.9	1.8	17.6
l-Isoleucine	0.6	1.2	11.7
l-Valine	0.6	1.2	11.7
l-Threonine	0.7	1.4	13.7
l-Cysteine	0.2	0.3	2.9
l-Histidine	0.2	0.3	2.9
l-Phenylalanine	0.1	0.2	2–0
l-Methionine	0.1	0.1	1.0
l-Tryptophan	0–1	0.1	1.0
Vitamin B1 (thiamine chlorhydrate)	0.0007	0.0001	0.0
Vitamin B6 (pyridoxine chlorhydrate)	0.0009	0.0002	0.0
Citric acid	0.409	0.82	8.0
Malic acid			1.92
Succinic acid	0.103	0.21	2.0
Total EAA (g)	4.5	9.0	100.0
Total mixture (g)	5.1	10.2	

Participants will take two sachets per day, orally, under the supervision of the nurse at mid-morning and midafternoon the day after the randomization. Boxes of the experimental sachets will be stored in a locked cabinet before administration in climate-controlled conditions and monitored weekly for consistency in ambient temperature.

The proposed formula consists of a complex blend of essential AAs, including some precursors of neurotransmitters that are important for regulating mood. In particular, phenylalanine, a precursor of tyrosine (non-essential AA), is involved in the biosynthesis of catecholamines (noradrenaline, adrenaline, dopamine), and tryptophan is the precursor of serotonin. Furthermore, the AAs of the mixture and the intermediates of the TCA cycle (citrate, malate, succinate) may stimulate mitochondrial bioenergetics by improving metabolism and muscle function.

#### Intensive treatment of eating disorders

The intensive treatment for EDs applied at the Department of Eating and Weight Disorders of Villa Garda Hospital has been described in previous publications [23–25]. The intervention is based on the enhanced cognitive behavioral therapy of eating disorders (CBT-E) [26], a treatment recommended by the National Institute for Health and Care Excellence guidelines for all eating disorders in adults and adolescents [2].

The treatment lasts 13 weeks and can be delivered in an inpatient or a day-hospital setting. The only difference between the two treatments is that in the day hospital, patients sleep outside the unit. Both treatments last 13 weeks and are delivered 7 days a week. The program is personalized to address the eating disorder psychopathology and its maintaining mechanisms operating in the patient. A distinctive characteristic of intensive CBT-E is its collaborative nature and the non-use of “coercive” or “prescriptive” attitudes or procedures. The goal is to engage patients in treatment and change throughout treatment actively. For this reason, admission to intensive CBT-E is collaboratively decided with the patients after three to four preparatory sessions. Since patients are expected to address weight restoration from the first day of the treatment, they must agree on this goal before they are admitted.

The main procedures of intensive CBT-E are shown in Table 2. These are delivered by a “non-eclectic” multidisciplinary team (physicians, psychologists, nurses, and dieticians) trained in the CBT-E. Clinical psychologists provide the procedures for addressing ED psychopathology in individual sessions, which occur twice a week in the first 4 weeks, once a week afterward, and twice in psychoeducational groups twice a week. A dietitian assists patients during meals until they achieve a BMI of ≥ 18.5. Physicians manage the patient’s physical health, and nurses supervise the administration of medications, assist patients in collaborative weighing, and help them to manage significant crises and daily difficulties. The last 3 weeks of the treatment are devoted to concluding the treatment well and preparing for the transition to outpatient therapy.

**Table 2 Tab2:** Core procedures and nutritional and physical rehabilitation protocols of intensive CBT-E

Core procedures
• Assisted eating (three meals and one snack a day)
• Weekly review meeting (with the clinical psychologist, dietician, nurse, and physician)
• Collaborative weighing one a week
• Individual CBT-E sessions
• Group treatment sessions
Nutritional rehabilitation protocol
• Weight goal: BMI ≥ 19
• Expected speed of weight gain: 1 to 1.5 kg per week
• Daily calorie content of the meal plan is established collaboratively with the patient according to the following guidelines:
—Week 1: Menu A (1500 kcal)
—Week 2: Menu B (2000 kcal)
—Afterward:
○ If the weight increases between 1 and 1.5 kg per week, the meal plan is maintained with the same calorie content as the previous week
○ If the weight increases to less than 1 kg per week, the meal plan is increased by 500 kcal per day. For example, from Menu B to Menu C (2500 kcal) or from Menu C to Menu D (3000 kcal)
○ If the weight increases more than 1.5 kg per week, the meal plan is reduced by 250 kcal per day. For example, from Menu C to Menu B / C (2250 kcal)
○ When the patient reaches a BMI of 19, the program’s goal is to identify a weight range of 3 kg that can be achieved without adopting a calorie restriction. In most patients, weight maintenance occurs with a diet between 2000 (Menu B) and 2500 kcal (Menu C)
Physical rehabilitation protocol
• All patients above a BMI of 15 participate in two 30-min sessions per week of calisthenics with a physiotherapist

*Abbreviations*: *BMI* Body mass index, *CBT-E* Enhanced cognitive behavioral therapy

### Criteria for discontinuing or modifying allocated interventions {11b}

Patients may withdraw from the trial at any time for any reason. The AmT-P mixture was demonstrated as safe and tolerable at the same dosage and length in malnourished older adults [20]. We do not anticipate that severe harm to require early product discontinuation or medical intervention. However, participants will be withdrawn by the team involved in the trial if they experience any new-onset, moderate, or severe adverse events from the intervention. The trial will be terminated if > 20% of all participants exhibit adverse events of moderate or great severity which are new from baseline or progressively worsening.

No intervention dose modifications or administration frequency changes are allowed. Participants will be considered non-adherent and withdrawn from the trial if deviations from the dosing standard are reported to the study team.

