### Composition of the data monitoring committee, its role and reporting structure {21a}

The data monitoring committee will be independent of the sponsor and will be composed of a medical doctor specialized in endocrinology, a medical doctor specialized in pharmacology, a psychologist, and a biostatistician. The data monitoring committee will review regular reports produced by the study team to ensure safe and responsible conduct of the trial and make any determination of discontinuation.

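### The safety premise of equal dose and duration conflicts with the protocol's own account of the cited study, and the only numeric termination trigger pools both arms without stating relatedness or denominator

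*Protocol article*

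**What the plan says.** **Safety premise.** Section {11b} of the protocol article relies on a cited study in older adults: "The AmT-P mixture was demonstrated as safe and tolerable at the same dosage and length in malnourished older adults [20]". The next sentence says that severe harm is not anticipated.

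**The cited study as the article describes it.** Under Background and rationale {6a}: "a recent randomized study was conducted for 2 months, in a double-blind, on 155 malnourished older adults", in which the active group "received a dietary supplement with a specific formula of EAA (8 g / day) plus nutritional advice".

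**This trial.** Intervention description {11a}: "The AmT-P blend will be administered orally at 4.5 g twice daily (two sachets per day". Table 1 gives, for two sachets, 9.0 g total essential amino acids (EAA) and 10.2 g total mixture. Trial design {8} sets treatment at 13 weeks.

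**Trigger.** Section {11b} ends the trial if more than 20% "of all participants exhibit adverse events of moderate or great severity which are new from baseline or progressively worsening".

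**Oversight.** Section {21a} sets up a data monitoring committee that is independent of the sponsor and includes a biostatistician. It "will review regular reports produced by the study team" and may decide on discontinuation. Section {17a} keeps everyone involved in trial conduct blinded until the primary analyses are complete. It gives the group code to staff who take no part in operations or analyses.

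**The concern.** There are two separate problems in the same section.

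First, the statement about prior safety does not match the article's own description of the study it cites, on dose or on duration. It matters because the expectation of no severe harm comes straight after it. An ethics or monitoring committee that relied on it would believe that this exposure had already been tested, in another population, when by the article's account the tested exposure was lower and shorter. Section {6b} meanwhile says that the research serves to establish safety.

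Second, the trigger responds to the overall event rate, not to a difference between arms. It counts participants in both arms together. It does not say whether events must be judged related to the product, although the individual-withdrawal rule just before it is limited to events from the intervention. Nor does it say whether the denominator is everyone planned, everyone enrolled so far, or those exposed. A pooled count can stay below the limit while events concentrate on active product, and can exceed it when the arms do not differ.

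**Working it through.** **1. Prior exposure against this trial**

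Inputs: 8 g/day and 2 months ({6a}); 4.5 g twice daily, with 9.0 g EAA and 10.2 g mixture per two sachets ({11a}, Table 1); 13 weeks ({8}). Assumption: 2 months = 2 × 365.25/12 = 60.9 days. The stated equality should give ratios of 1.

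| Quantity | Cited study | This trial | Ratio |
|---|---|---|---|
| Daily amount, EAA | 8 g | 2 × 4.5 = 9.0 g | 9.0/8 = 1.125 |
| Daily amount, if the 8 g meant total mixture | 8 g | 10.2 g | 10.2/8 = 1.275 |
| Duration | 60.9 days | 13 × 7 = 91 days | 91/60.9 = 1.49 |
| Cumulative EAA | 8 × 60.9 = 487 g | 9.0 × 91 = 819 g | 819/487 = 1.68 |

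The equality is not reproduced on either count, and reading the 8 g as total mixture widens the dose gap.

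**2. The trigger with all 92 as denominator**

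Inputs: 92 randomized, 46 per arm (Sample size {14}); limit above 20% ({11b}). Since 0.20 × 92 = 18.4, the trigger needs at least 19 participants.

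Splits that add up to 18 (18/92 = 19.6%) and so do not meet it, with the two-sided Fisher exact P:

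- 16/46 active (34.8%) against 2/46 placebo (4.3%): P = 0.0004.
- 18/46 active (39.1%) against 0/46 placebo: P about 0.000001.

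Chance of reaching 19 by the end of the trial. With equal rates, X ~ Binomial(92, p) and the chance is P(X ≥ 19). With unequal rates it is the sum of two binomials with n = 46 each. The documents give no event rates, so every rate here is an assumption.

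| Active rate | Placebo rate | Chance that the trigger is met |
|---|---|---|
| 20% | 5% | 1.6% |
| 30% | 5% | 24% |
| 35% | 5% | 48% |
| 40% | 5% | 72% |
| 20% | 20% | 48% |
| 25% | 25% | 86% |

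A 35% against 5% imbalance and no imbalance at 20% give the same 48%.

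**3. Why the denominator needs stating**

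Suppose the trigger is read as a running fraction of participants observed so far, with a true rate of 10% in both arms. The chance of ever exceeding 20% depends on when checking starts:

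| Checking starts at participant | Chance that the trigger is met |
|---|---|
| 10 | 21% |
| 20 | 12% |
| 30 | 7% |
| 46 | 3% |
| Only at all 92 | 0.2% |

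The starting points are illustrative. They show that one sentence permits rules with very different behaviour.

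**The case against.** **There are other ways to stop.** A reader might infer that this is the trial's only stopping mechanism. It is not. Section {21a} lets an independent committee determine discontinuation, section {11b} withdraws individuals for moderate or severe events from the intervention, section {17b} allows unblinding for severe events that lead to hospitalization or death, and section {22} provides biweekly grading, 24-hour reporting of serious events and ethics reporting within 15 days. This stands: it is the only numeric trigger, no more. Excess harm going unseen is a weakness of that rule, not a demonstrated failure of oversight as a whole.

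**By-arm reports are not ruled out.** A reader might also infer that the committee cannot see data by arm, because a blinded team writes its reports. The article does not say so. Independent staff hold the code, and a committee charter or the full protocol may provide for closed reports. This also stands. What can be said is that the reports are described only as produced by the study team, and that no by-arm review is stated.

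**The trigger may not be all-cause.** The wording does not say that events of any cause count. Section {22} has causality assessed for each event, and the trigger is limited to events that are new or worsening and at least moderate. Calling it all-cause would go too far; calling it unspecified is accurate.

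**A pooled limit can be deliberate.** It can serve as a blinded ceiling on overall tolerability, and pooling contradicts nothing in the article. That is fair. But such a ceiling does not detect an excess on active product, so by-arm review has to be provided for elsewhere.

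**The dose gap is small and no calculation uses the sentence.** The gap is 1 g/day, and neither the sample size nor the analysis depends on it. Both are true, and they limit the severity. The difference in duration is plain all the same, and the sentence supports the article's expectation about harm.

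**Conclusion.** The contradiction is certain and rests on the article alone: by its own account the cited exposure was about 1.1 times lower per day, 1.5 times shorter and 1.7 times lower in total (taking a month as 365.25/12 days). The documents do not show which section is in error, and nothing here says which dose or duration is right. Nor do they show that the cited formula was a different product: the background leaves it unnamed, and the Discussion cites the same study in a sentence about blends enriched with Krebs cycle intermediates.

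The weakness of the trigger holds in a limited form. As the only numeric rule, it pools arms and leaves relatedness and denominator open. With 92 as denominator it would not be met at 16/46 against 2/46, and it would be met 48% or 86% of the time at 20% or 25% in both arms. The threshold of 19 and the Fisher P values are exact for that denominator; the probabilities rest on assumed event rates. The point should be acted on, but it does not undermine the efficacy analysis.

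**What to change.** 1. Reconcile sections {6a}, {8}, {11a} and {11b}. State the dose, duration and product of the cited study as they were, next to those of this trial, and tell the ethics committee and the monitoring committee.
2. For the existing trigger, state whether it counts only events judged related to the product, and which denominator applies at each review.
3. State in {21a} that the independent staff who hold the group code supply adverse event counts by arm to the monitoring committee, while the trial team stays blinded. If a charter already provides for this, a cross-reference is enough.

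The cost is some wording, a notice to two committees, and a short by-arm table at each report, prepared by staff the trial already has. The dose, the 20% limit and the clinical rules are left as they are.
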